## 1. Background

Chronic heart failure (CHF) remains a major public health concern due to its increasing prevalence, high rates of hospital readmissions, and significant impact on patient morbidity and healthcare costs. Cardiac rehabilitation (CR) is a cornerstone in the management of CHF, aiming to improve functional capacity, reduce symptoms, and enhance quality of life (QoL) [1,2]. Despite its well-established benefits and strong recommendations from international guidelines, the uptake of CR remains suboptimal, often due to logistical, geographical, or psychosocial barriers [3,4]. In recent years, digital health technologies, including telerehabilitation, a subset of telemedicine that leverages information and communication technologies (ICT) to deliver rehabilitation services remotely, have emerged as promising tools to overcome these limitations [5]. This approach offers the opportunity to extend access to structured exercise programs and clinical monitoring beyond the hospital setting, while maintaining the standards of care required for patients with complex chronic conditions. Preliminary studies and pilot programs suggest that cardiac telerehabilitation (CTR) may offer clinical outcomes comparable to those of conventional center-based rehabilitation, with added advantages in terms of flexibility, patient engagement, and healthcare resource optimization [6]. Recent developments in remote care delivery and digital rehabilitation frameworks have contributed to a growing interest in structured, home-based programs that integrate technology-driven monitoring and personalized training components [7]. Nevertheless, high-quality evidence from real-world settings is still needed to support widespread implementation and to better understand which patient populations may benefit most from remote interventions [8,9].

Despite the growing body of evidence supporting cardiac telerehabilitation (CTR), current implementations still present important limitations. Most existing models are based on asynchronous exercise prescriptions, relying on self-reported adherence or commercial-grade devices with limited clinical validation [6,10,11]. These programs typically monitor a narrow set of parameters (e.g., heart rate or steps) without real-time supervision, which limits their ability to adjust exercise intensity based on physiological responses or to ensure patient safety [7,11,12]. Moreover, outcome measures are often restricted to functional performance, with few studies incorporating longitudinal assessments of biochemical, echocardiographic, or cognitive parameters [7].

In addition, current CTR protocols rarely consider the molecular dimension of exercise-based rehabilitation. The potential role of physical activity in modulating biomarker profiles—such as natriuretic peptides or inflammatory markers—remains largely unexplored in remote settings, and very few programs include the collection of biospecimens to analyze individual biological responses to training.

To address these limitations, the TELEREHAB-HF study introduces a technologically advanced, multidimensional, and translational approach. Through the integration of the Khymeia VRRS [13,14,15,16]—a clinically validated platform that enables real-time video supervision and multidomain physiological monitoring—our protocol ensures both remote safety and exercise accuracy. Moreover, by incorporating a “rehabilomics” framework [17,18], the study will investigate the biological correlates of training, thereby supporting the development of personalized rehabilitation pathways.

In summary, the TELEREHAB-HF study aims not only to confirm the clinical efficacy of home-based cardiac rehabilitation, but also to expand the scientific understanding of its impact across physiological, functional, cognitive, and molecular domains—bridging the gap between digital innovation and translational cardiology.

This protocol describes a prospective, controlled study designed to evaluate the efficacy of an 8-week home-based cardiac telerehabilitation program, supported by real-time remote monitoring technologies, in patients with CHF. The primary objective is to assess improvements in exercise capacity, measured via peak oxygen uptake (VO_2_max), compared to standard in-hospital rehabilitation. Secondary outcomes will include biochemical, functional, and QoL measures.

In addition, the study adopts a translational and “rehabilomic” perspective, aiming to explore the role of exercise as a modulator of specific molecular pathways involved in heart failure [19,20]. By identifying circulating biomarkers that are both pathophysiologically relevant and potentially responsive to physical training, the study seeks to contribute to the development of personalized rehabilitation strategies and a deeper molecular characterization of CHF patients [21].

## 2. Methods

### Study Design and Population

The TELEREHAB-HF study is a single-center, prospective, observational, non-pharmacological cohort trial designed to evaluate the clinical efficacy of a home-based, supervised cardiac telerehabilitation program in patients with CHF. The trial will be conducted at the tertiary care center Azienda Ospedaliera Universitaria (AOU) “San Giovanni di Dio e Ruggi d’Aragona” in Salerno, Italy, in collaboration with the University of Salerno. The study aims to enroll 220 adult patients (≥18 years) with a confirmed diagnosis of CHF—classified as heart failure with reduced ejection fraction (HFrEF), heart failure with mildly reduced ejection fraction (HFmrEF), or heart failure with preserved ejection fraction (HFpEF)—and functional class I to III according to the New York Heart Association (NYHA) classification. All participants must be clinically stable and on optimized medical therapy for at least one month prior to enrollment (Figure 1).

Participants will be allocated to the telerehabilitation or standard rehabilitation arm based on patient preference and logistical eligibility (e.g., home safety, access to digital devices, internet connectivity). Although this approach does not involve randomization, both groups will be enrolled under identical inclusion and exclusion criteria. To mitigate potential selection bias, comprehensive baseline characterization and statistical adjustment (e.g., propensity score methods) will be applied. Patients in the intervention group (TELEREHABILITATION-YES) will undergo an 8-week individualized cardiac rehabilitation program performed at home, supported by the Khymeia Virtual Reality Rehabilitation System (VRRS). The program includes real-time video-supervised sessions with a physiotherapist, and continuous monitoring through medical-grade wearable sensors that collect electrocardiogram (ECG), heart rate (HR), peripheral oxygen saturation (SpO_2_), and blood pressure (BP) data. The system also records exercise performance using inertial movement sensors, and all data are transmitted securely to a central digital platform for remote clinical oversight and feedback.

The collected clinical and biometric data will contribute to a translational and “rehabilomics” [17,18] framework, aiming to explore the impact of exercise on the molecular profile of CHF patients. Blood and urine samples will be collected and stored in a biobank for future analysis of biomarkers potentially modifiable by physical activity, thus supporting the identification of individualized rehabilitation strategies.

Patients in the control group (TELEREHABILITATION-NO) will follow a conventional 8-week hospital-based cardiac rehabilitation program under direct supervision. Sessions will be conducted at the outpatient cardiac rehabilitation facility and will include the same structure and intensity of exercise training as the intervention group. Vital signs and effort perception will be assessed and recorded manually using standard clinical tools.

All patients, regardless of group assignment, will undergo standardized evaluations at baseline, and at 4, 8, 16, and 24 weeks.

Prior to the intervention, each participant will undergo a comprehensive clinical evaluation performed by a cardiologist specialized in cardiac rehabilitation—who also serves as the head of the Cardiac Rehabilitation Unit at AOU “San Giovanni di Dio e Ruggi d’Aragona” in Salerno—including clinical examination, ECG, transthoracic echocardiography, and cardiopulmonary exercise testing (CPET) [22,23].

In parallel, physiotherapists will conduct a set of standardized functional assessments, including: 6-Minute Walk Test (6MWT), Short Physical Performance Battery (SPPB), Mini-Mental State Examination (MMSE) for cognitive screening, administration of health-related quality of life (HRQoL) questionnaires, including the Kansas City Cardiomyopathy Questionnaire—12 items (KCCQ-12) and the Short Form Health Survey—36 items (SF-36) [24,25,26,27].

This multidisciplinary assessment ensures that all participants are clinically stable, functionally and cognitively evaluated, and safely eligible to participate in either arm of the rehabilitation program.

Subsequent assessments will include laboratory analyses, including B-type natriuretic peptide (BNP), N-terminal pro B-type natriuretic peptide (NT-proBNP), Serum creatinine, electrolytes (sodium, potassium, chloride), lipid profile, blood glucose.

Additionally, anthropometric measurements—body weight, height, and body mass index (BMI)—will be recorded at each timepoint to monitor weight dynamics, which are clinically relevant indicators of fluid retention and potential decompensation in patients with heart failure [2,28].

Patients with NYHA class IV symptoms, severe renal impairment—defined as an estimated glomerular filtration rate (eGFR) < 30 mL/min/1.73 m^2^—terminal illness, pregnancy, inability to perform physical training, or insufficient digital literacy (in the absence of caregiver support) will be excluded (Table 1).

All clinical, instrumental, and biochemical data will be recorded in anonymized case report forms and stored in a secure, encrypted digital database. The study protocol complies with the Declaration of Helsinki and Good Clinical Practice (GCP) guidelines and has been approved by the Campania 2 Regional Ethics Committee (Approval Number: 14718 of 06.06.2024). The trial is registered at ClinicalTrials.gov under the identifier NCT07023536.

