## 3. Groups and Interventions

Participants enrolled in the study will be allocated to one of two groups based on their voluntary acceptance of the telerehabilitation modality:1.TELEREHABILITATION—YES (Remote Group)2.TELEREHABILITATION—NO (In-Person Group)

Both groups will undergo an 8-week individualized CR program based on international guidelines for heart failure rehabilitation [29]. The intervention includes a combined training protocol delivered 5 times per week for the first 4 weeks, and 3 times per week for the subsequent 4 weeks. Each session lasts approximately 60 min and is structured as follows (Table 2):10 min of interval training (warm-up) including flexibility, breathing, and coordination exercises;40 min of endurance training using a stationary bicycle, aiming at 70% of VO_2_ peak (as determined by baseline CPET) or 75–80% of maximum HR if CPET is not available [30,31,32,33,34];10 min of cool-down exercises with stretching and breathing techniques.

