## 9. Statistical Analysis

### 9.1. Primary Endpoint Analysis

To evaluate the primary endpoint of the study—defined as a ≥10% improvement in VO_2_max at 8 weeks—paired comparisons between baseline and post-intervention values will be performed using a paired t-test for normally distributed data [36,37,38]. For non-normally distributed data, the Wilcoxon Signed-Rank test will be applied. Additionally, the proportion of patients achieving the predefined VO_2_max improvement threshold will be analyzed using logistic regression, with “Rehabilitation Type (Telerehabilitation vs. Standard)” as the main predictor. The model will be adjusted for clinically relevant covariates identified through baseline comparisons using ANOVA or chi-square tests. Odds ratios and 90% confidence intervals will be reported.

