## 12. Study Limitations and Future Directions

This study has several limitations that should be acknowledged. First, the single-center design may limit the generalizability of findings, as patients are recruited from a single university hospital with specific technological infrastructure and clinical pathways. Future multicenter trials are needed to validate the model in more diverse healthcare settings and populations.

Second, the study does not employ randomized allocation to intervention and control groups, which introduces the potential for selection bias. Although careful matching and baseline characterization are planned to mitigate this issue, a randomized controlled trial would offer a higher level of evidence and should be considered in future research phases. Nevertheless, this pragmatic allocation strategy is particularly relevant in the context of the Salerno province, which includes geographically complex and low-accessibility areas such as the Amalfi Coast and inland Cilento. These regions are often underserved in terms of rehabilitation services. By allowing patients to choose their rehabilitation modality, the protocol increases accessibility and adherence, reflecting the real-world feasibility of implementing home-based telerehabilitation programs in underserved or hard-to-reach populations.

Third, the duration of follow-up (24 weeks), while longer than many previous CTR studies, remains insufficient to evaluate long-term outcomes such as rehospitalizations, cardiovascular events, or mortality. Extended follow-up studies will be necessary to assess the sustained impact and safety of the intervention over time.

Fourth, although the study includes multidimensional clinical and biological assessments, it does not incorporate a formal cost-effectiveness analysis, which is crucial for informing health policy decisions and large-scale implementation. The economic sustainability of the proposed model should be evaluated in subsequent studies.

Fifth, while body weight, height, and BMI are routinely collected and monitored throughout the study, more advanced measures of body composition—such as visceral adiposity—are not included. Considering that fluctuations in body weight are a recognized predictor of heart failure decompensation, this parameter remains clinically relevant and will be carefully analyzed, although the lack of imaging-based adiposity assessment represents a limitation.

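### Arm is decided by preference and home logistics, but the listed baseline data and the Section 9.1 adjustment reach these drivers only through clinical proxies, and patients ineligible for telerehabilitation can enter the comparison

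*Protocol article*

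**What the plan says.** **How the arm is set.** Section 2 (Study Design and Population) has patients "allocated to the telerehabilitation or standard rehabilitation arm based on patient preference and logistical eligibility (e.g., home safety, access to digital devices, internet connectivity". Section 3 describes them as "allocated to one of two groups based on their voluntary acceptance of the telerehabilitation modality", with no mention of logistics. Section 12 justifies letting patients choose by pointing out that the province "includes geographically complex and low-accessibility areas such as the Amalfi Coast and inland Cilento".

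**How selection is to be handled.** There are three descriptions:
- Section 2: "comprehensive baseline characterization and statistical adjustment (e.g., propensity score methods) will be applied".
- Section 9.1, for the logistic model: "The model will be adjusted for clinically relevant covariates identified through baseline comparisons using ANOVA or chi-square tests".
- Section 12: matching and baseline characterization.

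Section 9 mentions neither a propensity score nor matching.

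**What is listed at baseline.** Section 2 itemises a cardiology work-up, "including clinical examination, ECG, transthoracic echocardiography, and cardiopulmonary exercise testing (CPET", followed by 6MWT, SPPB, MMSE, KCCQ-12, SF-36, laboratory tests and anthropometry. Section 5 and Table 3 repeat these domains. Section 2 describes the case report form contents as clinical, instrumental and biochemical.

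**Eligibility.** Section 2 calls the criteria identical for both groups and lists insufficient digital literacy without a caregiver as an exclusion, with no limit to one arm. Table 1 applies that criterion to the tele-group only.

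**The concern.** The comparison is not randomised, so its credibility depends on adjustment for whatever both steers patients to an arm and predicts their response. The article names the steering factors, itemises the baseline data and states the adjustment set for the primary model, and the three do not fit together. Travel burden, caregiver support and digital competence could plausibly affect attendance at the 32 planned sessions (5 × 4 + 3 × 4) and therefore the VO2max gain. If they do, balancing the arms on disease severity alone leaves part of the arm difference attributable to who chose what. The sign of that bias cannot be told from the document.

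A second problem is overlap. A patient whose home or connectivity rules out telerehabilitation can only be in the in-person arm. No weighting or matching can supply a comparable remote patient for someone whose probability of being remote is zero.

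**Working it through.** **Step 1. Drivers of arm against listed baseline items.**

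| Driver | Status in the article | Among listed T0 items? |
|---|---|---|
| Preference / acceptance | decides arm (Sections 2 and 3) | no |
| Home safety | decides arm (Section 2) | no |
| Access to devices | decides arm (Section 2) | no |
| Internet connectivity | decides arm (Section 2) | no |
| Hard-to-reach residence | rationale for offering choice (Section 12), not an allocation rule | no |
| Digital literacy / caregiver | screened; tele-group only in Table 1 | no, eligibility check only |

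Of the first five, none appears among the listed items.

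**Step 2. Size of a missed driver (illustration; only the 200 patients and the two-sided 0.05 level come from Section 9.3).** Assume no true arm effect, 100 per arm, responders averaging 50%, and one unrecorded binary driver U, unrelated to the recorded covariates and with the same effect in both arms. With driver–response odds ratio ψ, the response probabilities are p0 and p1 = 1 − p0, where (p1/p0)² = ψ. If U is present in a proportion a of one arm and b of the other:
- arm rates: r1 = a·p1 + (1 − a)·p0 and r0 = b·p1 + (1 − b)·p0;
- spurious odds ratio: [r1/(1 − r1)] / [r0/(1 − r0)];
- SE of the log odds ratio: √[1/(100·r1(1 − r1)) + 1/(100·r0(1 − r0))], about 0.28 in every row.

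| ψ | a v b | p1 v p0 | r1 v r0 | Spurious OR | log OR / SE | P(p < 0.05) |
|---|---|---|---|---|---|---|
| 1.5 | 0.6 v 0.4 | 0.551 v 0.449 | 0.510 v 0.490 | 1.08 | 0.29 | 6% |
| 2 | 0.7 v 0.3 | 0.586 v 0.414 | 0.534 v 0.466 | 1.32 | 0.97 | 16% |
| 2 | 0.8 v 0.2 | 0.586 v 0.414 | 0.551 v 0.449 | 1.51 | 1.45 | 31% |
| 3 | 0.7 v 0.3 | 0.634 v 0.366 | 0.554 v 0.446 | 1.54 | 1.51 | 33% |

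**Step 3. How much clinical proxies recover (simulation, assumed inputs).** Here U is continuous, with odds ratio 2 per SD on both arm and response. X is a recorded clinical covariate with coefficient 0.3 on both log-odds scales. The true effect is zero and there are 400,000 simulated patients. The spurious risk difference is:

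| Correlation of U with X | Crude | Propensity on X | Propensity on X and U |
|---|---|---|---|
| 0 | 0.115 | 0.100 | 0.003 |
| 0.3 | 0.131 | 0.086 | −0.001 |
| 0.6 | 0.150 | 0.064 | 0.001 |

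Over odds ratios of 1.5 to 3 and these correlations, the bias left after weighting on X alone ranges from 0.024 to 0.199. If U affects the arm but not the outcome, it is about zero (−0.002).

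**Step 4. Price of modelling strong predictors of arm.** Take the stated 90% power at 200 patients as given (no SD or response rate is stated, so it cannot be reproduced). If covariates explain a share R² of arm variance, the effective size is about 200·(1 − R²) and the number needed about 200/(1 − R²).

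| R² | Power at 200 | Evaluable patients for 90% |
|---|---|---|
| 10% | 87% | 223 |
| 20% | 83% | 250 |
| 30% | 77% | 286 |
| 50% | 63% | 400 |

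**The case against.** The strongest reply is that this argues from silence in a condensed article. The list of assessments is introduced as inclusive, Table 3 is an outcome schedule, and age and NYHA class are not listed as baseline measurements either, though eligibility requires them. Logistical eligibility must be assessed in order to allocate, and digital literacy or caregiver support is screened. This stands to the extent that non-collection is not shown. A reader might infer that the promised propensity score cannot model selection at all. The document does not support that: the full case report form may hold the items, and MMSE, SPPB, 6MWT and NYHA class may carry part of the signal (Step 3). A reader might also infer that geography decides the arm, but Section 12 gives it only as a reason for offering choice.

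It is also fair that every magnitude is assumed and that the range starts at negligible. Distance would probably act mainly through attendance in the in-person arm, which the equal-effect model in Step 2 does not represent.

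Section 2 says the assessment makes all participants safely eligible for either arm. The assessments listed there are clinical, functional and cognitive, so this does not answer the logistical part.

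What the reply leaves untouched is a mismatch within the text. The stated allocation drivers do not appear in the stated adjustment for the primary model, which concerns clinical relevance and baseline tests, and the three descriptions of how selection will be handled differ.

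**Conclusion.** The concern holds in a limited form. Following the text as written, adjustment captures the drivers of choice only through clinical proxies. Residual confounding is likely for any driver that also predicts VO2max response; a driver that is not prognostic does no harm. Overlap fails for patients who were never eligible for telerehabilitation. Table 1 confirms the asymmetry for digital literacy, against the claim of identical criteria, and the logistical conditions in Section 2 create the same problem by themselves.

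The actual bias in this study, including its direction, cannot be derived from the document. The spurious odds ratios of 1.08 to 1.54 and rejection rates of 6% to 33% are illustrations only. They assume one unrecorded driver, equal arms, 50% responders and no correlation with recorded covariates. Correlated covariates reduce the bias without removing it. The change should be made, because the remedy is cheap and data collection is ongoing.

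**What to change.** 1. At T0, in both arms, record eligibility for telerehabilitation, reason for allocation, travel time to the unit, caregiver at home, digital literacy and employment. If the full case report form already holds these, name and use them.
2. Restrict the between-arm primary contrast to patients eligible for both modes, or at least prespecify this as a sensitivity analysis.
3. Fit one propensity model containing the prespecified prognostic drivers (travel time, caregiver, digital literacy, employment) and the clinical covariates. Do not select terms by baseline tests.
4. Use reason for allocation and remote ineligibility to define the analysis population, not as propensity terms. They nearly determine the arm and would push propensities to 0 or 1.
5. Reconcile Sections 2, 9.1 and 12 to this one method, and reconcile the identical-criteria statement in Section 2 with Table 1.

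**Cost.** A few baseline questions and revised wording. Precision is lost in two ways: modelling predictors of arm (Step 4 gives the order of size) and excluding remote-ineligible patients, whose number is not known. Patients already enrolled would have to be asked retrospectively, which is less reliable and should be reported as such.
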